##### Drug distribution and recovery

The control group is responsible for the distribution of the trial drug by the treatment physician. The patient is only given a 1-week drug quantity when entering the group. The kit is recovered by the observer during the follow-up visit, and the drug application registration form is filled in according to the judgment of the drug application situation. When the amount reaches 80–100% of the required amount of drug, the next course of the drug can be given according to the pain relief situation if the patient needs to continue the treatment. At the end of each course of treatment, each patient needs to recover the kit, and fill in the daily and each course of treatment on the medication registration form.

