### Interventions

#### Intervention description {11a}

##### Trial group

The main intervention method in the trial group is Shi’s cervical manipulation therapy. The manipulation treatment team is composed of six clinicians (two in each of the three trial centers) with a minimum of 5 years’ experience in manual operation, who are good at manual spine diagnosis and treatment and have received standard operating procedures (SOP) training in this study. Each selected subject should have a 3-dimensional (3D) computed tomography (CT) reconstruction of the cervical vertebra, as well as a special physical examination of the cervical vertebra. Each subject will receive an initial diagnosis for 15–20 min after entering the group, including brief history collection, cervical static palpation (tenderness point and muscle spasm), cervical dynamic palpation (intervertebral looseness of the cervical spine), cervical sequence activity inspection, and cervical nerve reflex. Both history and examination results should be recorded in the case report form. According to the examination results, manipulation clinicians will give a comprehensive diagnostic analysis and manipulation therapy to each subject’s cervical spine. Key points of manipulation therapy operation are as follows: (1) acupoint pressing analgesia operation, according to the treatment principle of local acupoint selection and remote acupoint selection of cervical vertebra; point rubbing; and pressing operation are performed on the thumb pulp. The pressure can be light to heavy, then heavy to light, and the operation is repeated. The specific strength is to press until thumb nail color is white, while considering patient tolerance. Each acupoint is operated for 1 min. The specific acupoints are as follows: (a) local acupoints—Fengchi (International acupoint code GB20), Fengfu (International acupoint code DU16), Tianzhu (International acupoint code Bl10), Wangu (International acupoint code GB12), Dazhui (International acupoint code DU14), Jianjing (International acupoint code GB21), Jianzhongshu (International acupoint code SI15), Quepen (International acupoint code ST12), Tianzong (International acupoint code Si11), and Ashi; (b) remote acupoints—Lieque (International acupoint code LU7), Houxi (International acupoint code SI3), and Hegu (International acupoint code LI4). (2) Bone-setting manipulation operation, according to the results of palpation and 3D CT reconstruction of the patient’s cervical spine, the clinicians will give directional and fixed-point bone-setting manipulation to treat the cervical vertebrae semidislocation. The specific operation is as follows: the patient sits on the treatment chair, with the head slightly bent forward, and the manual operation physician stands at the patient’s side, with the right side as the patient’s side, for example, the manual operation physician locks his left thumb against vertebral plate between the transverse process and the spinous process of the cervical vertebra with semidislocation, and the other four fingers stick to the patient’s left head and neck, and the middle and upper part of the elbow of the right arm slightly bent on the patient’s lower jaw, according to the vertebrae semidislocation direction, the left thumb with pushing force to the vertebral plate in the opposite direction of semidislocation, while the right forearm rotates rapidly to lift and rotate the head with a direction- and size-controlled flashing force. There is a sliding motion and snapping sound from the vertebra under the left thumb. The whole manual operation treatment lasts for 20 min each time, and is done twice a week, with the longest course of treatment lasting for 12 weeks.

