#### Outcomes {12}

##### Effectiveness evaluation index

The manual intervention program was pre-tested in our research group’s experimental study and was in effect immediately after the shortest treatment, and the longest treatment time was 12 weeks. Combined with the reported literature on related neck pain [14, 15], both groups are treated according to the main intervention methods of each group for a period of up to 12 weeks. Clinical data will be collected before the intervention and immediately after the first treatment; at 3 days and 1, 2, 4, 8, and 12 weeks after the intervention; and at 26 and 52 weeks after treatment follow-up of clinical observation index data collection. The clinical observation indexes are as follows: (1) cervical pain is the primary observation index, measured by NRS [16] and composed by a horizontal line with a length of 0–10 cm, and the anchor words are “0” for “no pain” and “10” for “extreme pain.” Participants are asked to select a point on the NRS line segment that corresponds to their current or recent week’s average pain intensity and draw a vertical line as a marker to express the pain intensity. The researchers determine the NRS score by measuring the distance from the starting point of “painless” to the marker point; the higher the score is, the stronger the degree of pain is. The specific judgment is as follows: 1–3 cm is mild pain, 4–6 cm is moderate pain, and 7–10 cm is severe pain. The secondary indices include the following: (2) cervical dysfunction index, measured by patient self-evaluation with cervical NDI [17, 18], which has 10 items in total, six options under each item, from light to heavy, corresponding to the score of 0–5, the lowest score of each item is 0, and the highest score is 5; the higher the score is, the more serious the degree of dysfunctions. NDI (%) = [(total score)/(number of items completed by subjects × 5)] × 100. The specific judgment is as follows: 0–20% indicates mild dysfunction, 21–40% indicates moderate dysfunction, 41–60% indicates severe dysfunction, 61–80% indicates extremely severe dysfunction, and 81–100% indicates complete dysfunction (whether subjects have exaggerated symptoms should be checked in detail); (3) cervical activity measurement [19], measured by the cervical vertebra mobility measurement program of Android mobile phone system, with a minimum of 5 degrees carry measurement; (4) overall improvement, measured by self-evaluation of patients with SF-36 (The Medical Outcomes Study 36-Item Short-Form Health Survey) [20, 21], which is composed of physical functioning, role-physical, bodily pain, general health, vitality (VT), social functioning (SF), role-emotional, mental health, and health transition; and (5) satisfactory treatment, determined by patient self-evaluation, is 1 of 3 levels: dissatisfied, satisfied, and very satisfied.

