#### Assignment of interventions: randomization

##### Sequence generation {16a}

In this project, a multicenter positive-controlled, randomized clinical trial design is adopted, and subjects who meet the test and research criteria are randomly divided into two groups (proportion of 1:1), which are the trial group and the control group. The random number table was generated by special statistical staff at Shanghai University of T.C.M. According to strict random procedures by using the SAS software (version 9.4, SAS Company, Cary, NC, USA). The randomized list is stored on a secure database (Microsoft Office Access 2007) by the data manager and is inaccessible by the relevant case observer or other researchers. Each subject can only register and randomize once, and no detailed information about the subject can be deleted from the database.

The design procedures of the specific randomized scheme of multicenter clinical trials include randomized parameter setting, randomized regulations, SAS-randomized program design, and the resulting random numbers, randomized coding of the trial center, randomized coding of the trial cases, and randomized coding of the treatment group.
Randomization parameter setting

Seed number, the initial value of the random number, in this study is 151427.

The total number of cases is the sample size. Area group length × area group number = total number of cases: sample size 240 cases, area group length 4, and area group number 60.

Stratification number, taking the center (hospital) participating in the clinical trial as the stratification factor, because the number of cases completed by each participating clinical trial center cannot be determined in advance, the management method of “random center” is adopted in this study; that is, when subjects are enrolled, the person in charge of each participating research center immediately requests the random number and corresponding group code from the “random center” by telephone.

The number of test groups is divided into trial group and control group.

Distribution proportion, the number of samples in each treatment group, is allocated by 1:1.
(2)Randomization rules

Randomization rules for center code distribution

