##### Allocation and implementation {16c}

Upon participant enrollment, the diagnostic intervention physician is responsible for asking the person in charge of each participating clinical center for the random number and corresponding group information, and then the person in charge of each participating clinical center immediately asks for the random number and corresponding group code from the “random center” by telephone, and then the person in charge of each clinical center informs the patient of the random number, corresponding group code, and intervention measures by telephone or WeChat. The intervention physician shall not disclose the above information to the subject and the symptom and sign information collection physician.

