#### Data collection, management, and analysis

##### Data collection {18a}

The data involved in this project mainly include random grouping data, clinical baseline data, intervention symptoms and signs change, follow-up data, and results of statistical analysis data.

The random grouping data shall be provided by the researcher in charge of the random grouping of the project (random center) of Shanghai University of Traditional Chinese Medicine, and only the person in charge of each clinical research center has the right to obtain the data.

All clinical research centers are responsible for the diagnosis and screening of clinical baseline data, and the physicians are responsible for recording and collecting the data.

The person in charge of each clinical research center shall arrange full-time data collection personnel to collect the intervention symptoms, signs, and follow-up data. They shall not actively know the random grouping, intervention plan, and other information.

Statistical analysis results data are collected and provided by the researcher in charge of data statistical analysis (statistical center) of Shanghai University of Traditional Chinese Medicine, who do not know the random grouping and clinical intervention information. After clinical trial completion, the personnel from the “statistical center” will go to each clinical research center to find the person in charge of each subcenter to coordinate and collect the case observation form, record the observation form in the database, and lock it under the supervision of the general research director of the project and the project supervisor (not directly involved in the project research).

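### Drug kits, which only control patients have, are recovered by an undefined observer; if that person also collects outcomes, the intended assessor masking is lost from about week 1

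*Protocol article*

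**What the plan says.** All references are to the protocol article.

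- **Kit handling.** Under *Drug distribution and recovery*, dispensing belongs to the control arm's treating physician: "The control group is responsible for the distribution of the trial drug by the treatment physician". Recovery is given to someone else: "The kit is recovered by the observer during the follow-up visit". The drug registration form is then filled in from what is returned. The first supply lasts one week.
- **Who has a kit.** Under *Trial group*: "The main intervention method in the trial group is Shi’s cervical manipulation therapy". Study drug is described only under *Control group*, for at most 12 weeks.
- **Who collects outcomes.** *Data collection {18a}* has each centre head appoint "full-time data collection personnel to collect the intervention symptoms, signs, and follow-up data", and says of them: "They shall not actively know the random grouping, intervention plan, and other information".
- **Other statements on masking.** *Allocation and implementation {16c}*: "The intervention physician shall not disclose the above information to the subject and the symptom and sign information collection physician". *Concealment mechanism {16b}* lists the collectors of symptom and sign data among those unaware of the groups. *Sequence generation {16a}* says the randomisation list "is inaccessible by the relevant case observer or other researchers".
- **Formal blinding.** *Blind implementation {17a}* names only subjects and statistical analysts.

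**The concern.** Manipulation and capsules cannot be made to look alike, and *Allocation and implementation {16c}* has the centre head tell patients which intervention they will receive. Keeping the outcome collector unaware of the group is therefore the main safeguard that can work when measurements are taken. Blinding the statistician cannot repair a reading that has already been recorded.

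A written rule that puts a control-only object into the collector's hands would undo that safeguard in routine conduct. The outcomes at stake are those on which staff have some influence: cervical mobility, read from a phone program in 5-degree steps, and the primary pain score, for which "The researchers determine the NRS score by measuring the distance from the starting point". Expectation is a plausible source of bias, because the lead centre is home to the technique and the other two centres cooperate with it (*Study setting {9}*).

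**Working it through.** No stated figure depends on this point, so there is nothing to recompute. The check is a cross-reading of the sections.

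1. **Does a kit identify the arm?** Yes, when one is returned. Study drug is given only in the control arm, so a returned kit means control. Absence is weaker evidence: it points to manipulation, but a control patient who has stopped the drug also brings nothing.

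2. **Is the observer the dispensing physician?** No. *Drug distribution and recovery* names the treatment physician for dispensing and the observer for recovery, as two roles.

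3. **Is the observer the outcome collector?** This is not stated and has to be inferred. Three things support it:
   - The observer acts at the follow-up visit, where outcomes are taken.
   - *Data collection {18a}* calls the form collected for the database the case observation form.
   - *Data management {19}* has case observation doctors handling the collected case forms.

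   *Sequence generation {16a}* also uses the term case observer, for someone kept from the randomisation list.

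4. **Are collectors meant to be unaware?** Yes, by *Allocation and implementation {16c}* and *Data collection {18a}*, with support from *Concealment mechanism {16b}*. *Blind implementation {17a}* does not list them, so the article is not consistent on the point.

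5. **When could the arm become known?** There are nine scheduled assessments after baseline: immediately after first treatment, day 3, and weeks 1, 2, 4, 8, 12, 26 and 52.
   - With a one-week first supply and at most 12 weeks of drug, kits could come back at weeks 1, 2, 4, 8 and 12. That is at most 5 of 9.
   - No return is due immediately after first treatment, at day 3, or at weeks 26 and 52.
   - Knowledge persists once gained, so up to 5 + 2 = 7 of 9 assessments could be made by someone who knows the arm. The figure is 6 if the week-1 outcomes are taken before the kit is handed over; the article gives no order.
   - Week 12, the time point behind the pain scores in *Sample size {14}*, falls within this window.

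6. **Which outcomes are exposed?** Cervical mobility most. The NRS less, since the patient draws the mark and staff only measure its distance. NDI, SF-36 and satisfaction are self-rated and little affected by this route.

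**The case against.** The strongest reply is that the article never says the observer and the outcome collector are the same person. Elsewhere, observation wording goes with duties that involve knowing the treatment: a clinical observation physician decides on stopping after an adverse reaction, and the case observation form records compliance and last treatment time. The observer could be a separate, unmasked member of staff. This stands as a limit on certainty. It does not remove the point, because the article gives no such separation and most of its wording points the other way.

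Further objections narrow the claim:

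- The list restriction in *Sequence generation {16a}* concerns access to the sequence, not masking after assignment, so it cannot carry the argument alone.
- *Concealment mechanism {16b}* also lists intervention physicians as unaware, which cannot hold once they treat.
- The wording in *Data collection {18a}* bars seeking the information and does not guarantee ignorance of it.
- *Study setting {9}* ties the technique to one centre with two collaborators, not to all three.

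A procedure manual exists and may separate the roles. But the issue here is a stated rule that points the wrong way, not a missing detail, and a possible manual entry does not cure it.

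A reader might also infer that masking fails at every visit, or that the 5-degree step measures the bias. The documents support neither. Kits return only during the drug period, and 5 degrees is the resolution of the instrument, not an estimate of assessor error.

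**Conclusion.** The concern holds in a limited form. As written, kit recovery conflicts with the intended masking of outcome collectors, provided the observer is the person who collects case data. That is a reasonable inference from the article, not something it states. On that assumption, the arm of control patients becomes known from about week 1, while drug is taken, and stays known afterwards. The exposure falls mainly on cervical mobility, a secondary outcome, and to a lesser degree on the measuring of the NRS mark.

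A reader might go further and conclude that the primary result is biased in favour of manipulation. The documents do not support that: they give nothing from which a size of bias could be calculated, and the patient, not the assessor, places the pain mark. The change is nevertheless worth making, because the leak is avoidable and cheap to close.

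**What to change.** - In *Drug distribution and recovery*, assign kit recovery and the drug registration form to the control-arm treatment physician, to be done after the outcome assessment at that visit.
- Keep kits, patient log cards and the medication form away from the outcome collector, and ask patients not to show them.
- Define the observer, and reconcile *Blind implementation {17a}* with sections {16b}, {16c} and {18a} on whether assessors are masked.
- For visits already held under the current rule (*Trial status* gives recruitment as starting on 30 October 2019), do not report assessors as unaware of allocation.

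**Cost.** A sentence or two in the protocol and a line in the operating procedures, with no new staff or visits and a few more minutes for the treating physician. There is one small downside: the physician who dispenses the drug would also make the count that feeds the 80–120% compliance rule for the per-protocol set (*Statistical methods {20a}*). The case supervisor's existing spot checks (*Data management {19}*) can cover that.

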
##### Control group

The main intervention method in the trial group is oral NSAIDs. Each selected subject should have a 3D CT reconstruction of the cervical vertebra, as well as a special physical examination of the cervical vertebra. The treatment team is composed of three clinicians (one in each of the three trial centers) with the qualification of clinical medical registered doctors and senior professional titles, who have received SOP training in this study. After exclusion of the contraindications of diclofenac sodium (known to be allergic to other components of diclofenac sodium, acetylsalicylic acid, ibuprofen, and Daphne, gastric and duodenal ulcer, gastrointestinal inflammatory disease, black stool, or unknown blood history), the NSAID diclofenac sodium double-release enteric-coated capsules (Difene, manufacturer Temmler Ireland. Ltd.; 75 mg, once a day, once a time, oral) is the main intervention. Each subject will receive an initial diagnosis for 15–20 min after entering the group, including brief history collection, cervical static palpation (tenderness point and muscle spasm), cervical dynamic palpation (intervertebral looseness of the cervical spine), cervical sequence activity inspection, and cervical nerve reflex. Both history and examination results should be recorded in case report form. Each subject will obtain a patient log card, which shall be kept by the patients themselves (handed over to the physician in charge of the group at the end of the test), and will be used to record name, dose, time, discomfort, combined medication, and other information about the drug taken truthfully every day. The specific drug dosage shall be specified by the physician in charge of the group according to the drug use instructions, and the maximum duration of the medication shall be 12 weeks.

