#### Criteria for discontinuing or modifying allocated interventions {11b}

Participants may request to leave the study or they may be withdrawn due to study-related adverse events and shedding criteria. If a subject is discontinued from study participation due to an adverse event, they will be evaluated by the study clinicians for the need of additional treatment for neck pain. Safety data will be collected on any subject who is withdrawn from the study. Participants in both study groups may receive additional treatment. Emergency treatment for patients who have severe pain and cannot tolerate manipulation therapy or cannot improve their pain within a short period of time affecting their sleep or life should be given emergency analgesic or sedative, muscle relaxant drugs, and then be rejected from the trial.

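### Read literally, the dispensing rule makes further diclofenac depend on 80–100% intake as well as need, with no comparable condition on further manipulation sessions

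*Protocol article*

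**What the plan says.** The supply rule for the control arm is under Drug distribution and recovery. It starts small: "The patient is only given a 1-week drug quantity when entering the group". The observer recovers the kit at the follow-up visit and judges how much was taken. The rule for more drug follows: "When the amount reaches 80–100% of the required amount of drug, the next course of the drug can be given". A need condition is attached to it in the same sentence: "according to the pain relief situation if the patient needs to continue the treatment".

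The Control group section sets the dose at "75 mg, once a day, once a time, oral" and the ceiling: "the maximum duration of the medication shall be 12 weeks".

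For manipulation, the Trial group section says only that treatment "is done twice a week, with the longest course of treatment lasting for 12 weeks". It gives no attendance figure for receiving the next session.

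Section {11b} adds: "Participants in both study groups may receive additional treatment". A patient whose severe pain calls for emergency treatment is to receive "emergency analgesic or sedative, muscle relaxant drugs, and then be rejected from the trial". Section {11d} disallows other painkillers in principle, with a recorded exception for special situations. Sections {11d} and {20c} respond to poor compliance by recording the reasons and contacting the patient. Neither says whether drug is then supplied.

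**The concern.** The need condition is sound: a patient whose pain has gone should not be given more diclofenac. The difficulty is the intake condition beside it. A patient who still has pain and still wants treatment can fall short of the stated condition because of a few missed capsules. The protocol gives no other basis for resupplying that patient.

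The trial is sized on NRS pain after 12 weeks (Sample size {14}), and its hypothesis is that manipulation does better than the drug. If a site applied the sentence literally, some control patients could stop receiving the comparator before that assessment for a reason other than lack of need, intolerance or their own choice. No equivalent condition acts on manipulation. Less comparator exposure would tend to worsen control-arm pain and so favour manipulation on the primary outcome. With three centers dispensing, the sentence could also be applied differently from one to another.

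**Working it through.** No sample size, power or alpha figure is involved, so there is no plan figure to reproduce. The check is a comparison of the continuation rules, plus a capsule count.

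**Inputs**
- Dose: one 75 mg capsule a day (Control group).
- Entry supply: one week (Drug distribution and recovery).
- Condition for the next course: 80–100% of the required amount, and need (same section).
- Manipulation: two sessions a week, at most 12 weeks (Trial group).

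**Capsule count for the first supply**
- Required amount: 7 days × 1 capsule = 7 capsules.
- Threshold: 0.80 × 7 = 5.6 capsules.
- 6 of 7 = 85.7%: meets the condition.
- 5 of 7 = 71.4%: does not.

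Two missed capsules in the first week are therefore enough. The length of later courses is not given, so the count is not extended beyond the first supply.

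**Manipulation arm**
- A patient attending 1 of 2 sessions in week 1 has 50% attendance. No figure in the Trial group section bears on whether the next session is given.

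**Rules on continuing treatment, side by side**

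| Rule | Section | Arm | Numeric? | Condition for further treatment? |
|---|---|---|---|---|
| 80–100% intake, plus need | Drug distribution and recovery | Control | Yes | Yes, as worded |
| 12-week maximum | Trial group; Control group | Both | Yes | No; an equal ceiling |
| Rejection for not following treatment strictly | Rejection criteria | Not limited to one arm | No | Removes a patient; sets no threshold |
| Shedding for withdrawal or missed visits | Shedding criteria | Not limited to one arm | No | Same |
| 80–120% of drug | Statistical methods {20a} | Drug use | Yes | No; defines the per-protocol set |

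The only numeric condition for receiving more treatment is in the comparator arm.

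**Can the frequency be estimated?** The document gives no adherence figure. Purely as an assumption, let each daily capsule be taken independently with probability p. The chance of meeting the first-week condition is then p⁷ + 7p⁶(1 − p):

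| p (assumed) | Chance of meeting it |
|---|---|
| 0.80 | 0.58 |
| 0.85 | 0.72 |
| 0.90 | 0.85 |
| 0.95 | 0.96 |

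The result depends almost entirely on the assumed p. It also does not say how many of those below the threshold would still be in pain, or would actually be refused. The conclusion does not use these values.

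**The case against.** **It may be only a resupply trigger.** The sentence could mean that a new pack is issued once the current one is nearly used up. The wording about the amount reaching a level, and the 100% upper limit, lend this some support. On that reading, a patient who took 5 of 7 capsules takes one more and is resupplied. It fits poorly with the rest of the paragraph, because the kit is recovered at the visit where intake is judged, so no leftover capsules remain to finish. The ambiguity is real, though, and is itself a reason to reword.

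**Refusal is not stated.** This stands. The wording is permissive, and no section says that a patient below 80% is turned away. A reader might infer that one poor week costs the other 11 of 12 weeks, which is 84 − 7 = 77 of 84 capsules (92%). That requires permanent exclusion after a single check, which the document does not state, so the figure should not be used as a measure of the problem.

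**Low intake may be handled in the SOP or investigator's manual.** These exist and are not shown, and their detail is not missing from an article. The point here is the condition that the article prints, not an absent procedure.

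**Adherence rules apply to both arms.** This stands in part. The Rejection and Shedding criteria could remove a poorly adherent manipulation patient too. The asymmetry is confined to the numeric condition for further treatment. Take-home capsules also need accountability in a way that clinic sessions do not. That justifies counting capsules, but not making supply depend on the count.

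**The direction of bias is selective.** This also stands in part. Less diclofenac would tend to mean fewer drug adverse events in the control arm, which works against the safety hypothesis. A patient below the threshold is already taking less drug, so the further loss due to the rule is unknown. The directional statement is therefore limited to pain.

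**Conclusion.** The point holds as a cheap improvement to the wording. Read literally, the protocol makes the next diclofenac course conditional on 80–100% intake as well as need. A control patient still in pain who took 5 of 7 capsules (71%) does not meet that condition, and there is no comparable condition for the next manipulation session.

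This rests on taking the sentence as a condition and on a dose of one capsule a day. Neither the number of patients affected nor any shift in NRS can be derived, and none is claimed. What can be said is directional: any comparator exposure lost this way would tend to favour manipulation on pain.

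A reader might go further and conclude that the trial is built to deprive controls of treatment. The document does not support that. Resupply also depends legitimately on need, additional treatment is allowed in both arms, poor compliance is met with contact and support, and the general adherence rules are not limited to one arm.

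**What to change.** Under Drug distribution and recovery, replace the 80–100% condition with:

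> The next course is given while the patient still needs and tolerates treatment, up to 12 weeks in total. If intake was below 80%, the reason is recorded and the patient is contacted as under {11d}; drug is not withheld for this reason.

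Under Rejection criteria, state that low intake alone is not a ground for rejection. Otherwise that section could bring back the exclusion that the new wording removes.

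Continue to count capsules at kit recovery, but use the counts only to define the per-protocol set, with the 80–120% window in Statistical methods {20a} unchanged. The Trial group section needs no edit, since it states no condition to correct.

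The cost is the replacement wording, one clarification, and a matching change to the site dispensing instruction. No patients, staff, visits or procedures are added. The downside is that some drug is dispensed to patients with poor adherence.
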